|          |                     | 19%            | cataract        |
|          |                     | 37%            | microvascular   |
|          |                     | 43%            | PVD             |

| Steno 13 year FU       | SC=80 | UC=80 | HR   |
|------------------------|-------|-------|------|
| death                  | 24    | 40    | 0.50 |
| CVD-death              | 9     | 18    | 0.23 |
| MI                     | 8     | 21    | 0.26 |
| stroke                 | 6     | 18    | 0.23 |
| PCI                    | 8     | 13    | 0.16 |
| revascularization      | 6     | 10    | 0.13 |
| amputation             | 6     | 14    | 0.18 |
| all CVD events         | 25    | 48    | 0.60 |
| cancer-death           | 2     | 5     | 0.06 |
| DM nephropathy         | 20    | 37    | 0.46 |
| ESRD                   | 1     | 6     | 0.08 |
| Blindness              | 2     | 7     | 0.09 |
| Progression of DMR     | 41    | 54    | 0.68 |
| Laser or macular edema | 14    | 27    | 0.34 |

| 2-year SURE Study | ≥3 target | <3 targets | HR   |
|-------------------|-----------|------------|------|
| ESRD/death/dSeCr  | 14        | 34         | 0.30 |
| dialysis          | 6         | 12         | 0.11 |
| dSeCr             | 10        | 21         | 0.18 |
| death             | 4         | 15         | 0.13 |
| MI/angina/PCI     | 4         | 7          | 0.06 |
| heart failure     | 12        | 16         | 0.14 |

| 7-year AJMC paper | SC | UC | HR   |
|-------------------|----|----|------|
| death             | 8  | 20 | 0.25 |
| death/CVS/renal   | 20 | 30 | 0.38 |

These Kaplan-Miere plots show the estimated events from these 3 studies in a 2-year period.

Chinese T2D patients with CKD (eGFR 30 ml/min/1.73m^2)  
Chan JC et al Diabetes Care 2009

[figure not shown]

Chinese T2D patients with HT (no CVD/CKD)  
So WY et al Am J Managed Care 2003

[figure not shown][figure not shown]

Caucasian T2D patients with microalbuminuria (no CVD/CKD)  
Gaede P et al NEJM 2008

[figure not shown]

Using validated risk equations and risk parameters, the JADE Program stratified patients into very high risk, high risk, medium risk and low risk groups with respective estimated annual event rate of 7%, 3%, 1.5% and 1%.

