#### Complications and risk factors in 3687 Asian T2D patients

[figure not shown]

So WY et al for JADE Study Group J of Diabetes 2011

We used these observations to estimate the sample size needed to give a 2-year study 80% power with an alpha value of 0.05 to confirm the superiority of team-based structured care over usual care on clinical endpoints. We used different combinations of scenarios including an annual hazard rate ranging from 0.01 to 0.10 in the usual care group and a HR ranging from 0.5 to 0.85 in the structured care group with an attrition rate of 0.2, to estimate the sample size. Using the most conservative scenario where the annual hazard rate is 0.02, i.e. 0.04 in 2 years and assuming a HR of 0.8 in the structured care group, the study will have sufficient power to confirm the primary hypothesis. For high risk patients with a hazard rate of 0.05 and those with medium risk (0.03), and assuming a modest HR of 0.8 in the structured care group, a sample size of 6626-13762 patients will give the study 80% power at an alpha value of 0.05.

|                                                     |      |       |                |      |       |       |
|-----------------------------------------------------|------|-------|----------------|------|-------|-------|
| 80% power at 0.05 alpha
minimum 2 year follow up |      |       |                |      |       |       |
| LOW RISK                                            |      |       | VERY LOW RISK  |      |       |       |
| hazard ratio                                        | 0.5  | 0.8   | 0.85           | 0.5  | 0.8   | 0.85  |
| annaul hazard rate                                  | 0.02 | 0.02  | 0.02           | 0.01 | 0.01  | 0.01  |
| hazard rate (usual)                                 | 0.04 | 0.04  | 0.04           | 0.02 | 0.02  | 0.02  |
| hazard rate (structured)                            | 0.02 | 0.032 | 0.034          | 0.01 | 0.016 | 0.017 |
| absolute difference                                 | 0.02 | 0.008 | 0.006          | 0.01 | 0.004 | 0.003 |
| sanple size in each group                           | 1239 | 8760  | 15868          | 2515 | 17838 | 32333 |
| total sample size                                   | 2478 | 17520 | 31736          | 5030 | 35676 | 64666 |
| assuming 20% attrition rate                         | 2974 | 21024 | 38083          | 6036 | 42811 | 77599 |

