## **DATA ANALYSIS**

All data will be analyzed using the SPSS statistical software (Windows 13.0 version, Chicago, USA). A p value of 0.05 or less (2-tailed) will be considered significant. For the primary composite endpoint, an intention to treat analysis will be performed including all patients randomized to both groups who have at least returned for one visit or contacted by phone once post randomization to ascertain clinical status (alive, dead or hospitalized). Descriptive analysis will be used to report all clinical and laboratory parameters. Student's t-test, Chi-squared test and Analysis of Co-variance will be used for between-group and within-group comparisons for all baseline data and endpoints, as appropriate. Kaplan-Meier curve analysis will be used to compare the incidence of primary composite endpoint between the JADE and DIAMOND group adjusted for age, sex, ethnicity and disease duration. Interaction between group assignment and covariates including age, gender, duration of diabetes (< or ≥8 years), socioeconomic group, complications, risk factors, JADE risk categories, compliance and psychological health parameters will be examined. Logistic regression will be used to determine independent predictors for achieving primary composite endpoint using all relevant covariates including age, gender, duration of diabetes (< or ≥8 years), centre characteristics, socioeconomic group, risk levels, metabolic and risk factor control, compliance, self care, psychological health parameters and intervention groups.

A per protocol analysis will be performed in the JADE group with details of intervention, where we shall compare baseline clinical profile, care processes, number of visits and use of medications between patients who develop and those who do not develop clinical endpoints. A sensitivity analysis will also be performed using hazard rates of the JADE and DIAMOND group amongst those who have defaulted.

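### The sample size gives the high- and medium-risk groups annual event rates of 5% and 3%, where the same section has put them at 3% and 1.5%

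*Protocol*

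**What the plan says.** Under Sample Size Calculation, Primary composite outcome, the protocol reports that the programme's risk equations sort patients into "very high risk, high risk, medium risk and low risk groups with respective estimated annual event rate of 7%, 3%, 1.5% and 1" per cent. After the material on first-year enrolment it continues: "We used these observations to estimate the sample size needed to give a 2-year study 80% power". It describes a grid of scenarios, with annual usual-care rates from 0.01 to 0.10, hazard ratios from 0.5 to 0.85 and 20% attrition. The operative sentence reads: "For high risk patients with a hazard rate of 0.05 and those with medium risk (0.03), and assuming a modest HR of 0.8", and concludes that 6626-13762 patients give 80% power.

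The tables that follow label their blocks very low, low, moderate, high and very high risk, with annual rates of 1%, 2%, 3%, 5% and 10%. In the hazard ratio 0.8 columns, high risk shows 6626 before attrition and 7951 after. Moderate risk shows 11468 before and 13762 after. Data Analysis fixes the test: "A p value of 0.05 or less (2-tailed) will be considered significant".

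**The concern.** Within one section, the same risk labels carry two sets of event rates, and the set used for sizing is higher at every level:

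| Label | Rate from the risk equations | Rate used for sizing | Ratio |
|---|---|---|---|
| Very high | 7% | 10% | 1.4 |
| High | 3% | 5% | 1.7 |
| Medium / moderate | 1.5% | 3% | 2.0 |
| Low | 1% | 2% | 2.0 |

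For a fixed hazard ratio, the required number is nearly inversely proportional to the event rate, so every shift makes the trial look smaller than the section's own figures imply. The range 6626-13762 is the only total that the text gives for 80% power on the primary endpoint. Recruitment is set per site, at 600. The range is therefore what tells the sponsor how many sites are needed.

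**Working it through.** **Inputs.** Two-sided alpha 0.05 (Data Analysis), 80% power, 1:1 allocation (Setting and Patients), hazard ratio 0.8, 2-year proportion = 2 x annual rate, and the hazard ratio applied as a ratio of those proportions. The last two are how the tables work (for example 0.10 against 0.08). The tables apply attrition as N x 1.2.

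**Formula.** With d = p1 - p2 and pbar = (p1 + p2)/2:

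- n0 = [1.96 x sqrt(2 x pbar x (1 - pbar)) + 0.842 x sqrt(p1(1 - p1) + p2(1 - p2))]^2 / d^2
- with continuity correction, n = (n0/4) x [1 + sqrt(1 + 4/(n0 x d))]^2 per group

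**Step 1: reproduce the protocol at its sizing rates.**

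- High risk, 0.10 v 0.08: n0 = 3213, n = 3313 per group, total 6626; x 1.2 = 7951.
- Moderate risk, 0.06 v 0.048: n0 = 5568, n = 5734 per group, total 11468; x 1.2 = 13762.

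All match the tables exactly. The stated range therefore joins a total before attrition (6626) to a total after attrition (13762).

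**Step 2: same method, rates from the risk equations.**

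| Group | 2-year proportions | Per group | Total evaluable | x 1.2 | Printed under that label |
|---|---|---|---|---|---|
| High, 3% | 0.06 v 0.048 | 5734 | 11468 | 13762 | 6626 / 7951 |
| Medium, 1.5% | 0.03 v 0.024 | 11786 | 23572 | 28286 | 11468 / 13762 |

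The evaluable number rises by 73% (11468/6626 = 1.73) and 106% (23572/11468 = 2.06). At 600 per site, the post-attrition totals go from 7951/600 = 13.3 to 13762/600 = 22.9 sites, and from 22.9 to 28286/600 = 47.1 sites.

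**Step 3: power at the stated numbers.** Power = Phi{[d - 1.96 x sqrt(2 x pbar x (1 - pbar)/n)] / sqrt([p1(1 - p1) + p2(1 - p2)]/n)}. For the continuity-corrected value, d is replaced by d - 1/n. For example, 6626 analysed at 3% has n = 3313, d = 0.012 and both standard errors close to 0.00555. This gives (0.012 - 1.96 x 0.00555)/0.00555 = 0.20, and Phi(0.20) = 58%.

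| Patients | Annual rate | Uncorrected | Corrected |
|---|---|---|---|
| 6626 analysed | 5% (as sized) | 81% | 80% |
| 6626 analysed | 3% | 58% | 56% |
| 6626 less 20% (2650 per group) | 5% | 72% | 70% |
| 6626 less 20% | 3% | 49% | 46% |
| 13762 less 20% (5505 per group) | 3% (as sized) | 80% | 78% |
| 13762 less 20% | 1.5% | 49% | 47% |

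A log-rank (Schoenfeld) check, with 631 events needed, gives 56% for 6626 analysed at 3% and 49% for 13762 less 20% at 1.5%.

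**The case against.** **The tables are a scenario grid, not a restatement of the risk levels.** There are five blocks against four risk levels, and the observations relied on also include three earlier studies and figures not shown here. That is fair for the grid as a whole. It does not cover the operative sentence, which attaches 5% and 3% to high- and medium-risk patients shortly after the same section gave those groups 3% and 1.5%.

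**The primary composite may be broader than what the risk equations predict.** Outcome Measures includes hospitalised infection, all-site cancer, eye surgery, reduced eGFR and any death, and the protocol does not say that the lower rates cover all of this. This stands: the documents do not settle which rates are right. The protocol does not offer it as the reason, however, and its section on validating the risk equations assumes only 2% a year for a broad set of diabetes-related events.

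**The trial is not made up of one risk group.** Patients are consecutive, and the protocol says most first-year enrolees were at very high or high risk. A reader might infer from the 47-49% that the trial as a whole has about even odds of detecting its effect. The documents do not support that. If every patient had a 3% rate, 13762 less 20% would give 78-80%. If very high (7%) and high (3%) were mixed 50:50, which is an assumption, the average would be 5% and 6626 analysed would give about 80%.

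**A single figure of about 47% for the whole range is also tempting.** It fits only the upper end. At the lower end, the rate change alone takes power from 80% to 56-58%. Reaching 46-49% requires removing 20% from a number that never allowed for attrition, and on that basis power at 5% is already only 70-72%.

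**Conclusion.** The contradiction is real, and the readable text does not explain it. The printed numbers reproduce only at the higher rates, so the claim of 80% power for high- and medium-risk patients conflicts with the event rates given for those groups in the same section. At those rates the required number is about 1.7 times (high risk) and 2.1 times (medium risk) what is stated. Power at the stated numbers is about 56-58% for 6626 analysed high-risk patients, and about 47-49% for 13762 medium-risk patients after 20% loss.

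This rests on a hazard ratio of 0.8, the protocol's doubling of annual rates and its two-proportion method, and it applies within a single risk group. Power for the trial as a whole cannot be derived from the readable text, because neither the expected risk mix nor the average event rate is given.

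**What to change.** - Reconcile the two sets of rates in the sample size section. Either use the risk-equation rates under their own labels and restate the numbers and power (at hazard ratio 0.8, evaluable / x 1.2: very high 4550 / 5460; high 11468 / 13762; medium 23572 / 28286; low 35676 / 42811), or give a source for the higher rates as applying to the full composite and rename the table rows so that they do not reuse the risk-level labels.
- State the expected mix of risk levels and the average annual event rate that it implies, and base the trial's total on that average.
- Quote both ends of the range on the same attrition basis. As the tables stand, that would be 6626-11468 before attrition or 7951-13762 after.

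The cost is a correction of text and tables. If the lower rates are adopted, the stated sample size grows or the stated power falls. If the higher rates are kept, the sponsor has to document where they come from.

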| number needed to treat                              | 50   | 125   | 167            | 100  | 250   | 333   |
| MODERATE RISK                                       |      |       |                |      |       |       |
| hazard ratio                                        | 0.5  | 0.8   | 0.85           |      |       |       |
| annaul hazard rate                                  | 0.03 | 0.03  | 0.03           |      |       |       |
| hazard rate (usual)                                 | 0.06 | 0.06  | 0.06           |      |       |       |
| hazard rate (structured)                            | 0.03 | 0.048 | 0.051          |      |       |       |
| absolute difference                                 | 0.03 | 0.012 | 0.009          |      |       |       |
| sanple size in each group                           | 1067 | 5734  | 13820          |      |       |       |
| total sample size                                   | 2134 | 11468 | 27640          |      |       |       |
| assuming 20% attrition rate                         | 2561 | 13762 | 33168          |      |       |       |
| number needed to treat                              | 33   | 83    | 111            |      |       |       |
| HIGH RISK                                           |      |       | VERY HIGH RISK |      |       |       |
| hazard ratio                                        | 0.5  | 0.8   | 0.85           | 0.5  | 0.8   | 0.85  |
| annaul hazard rate                                  | 0.05 | 0.05  | 0.05           | 0.1  | 0.1   | 0.1   |
| hazard rate (usual)                                 | 0.1  | 0.1   | 0.1            | 0.2  | 0.2   | 0.2   |
| hazard rate (structured)                            | 0.05 | 0.08  | 0.085          | 0.1  | 0.16  | 0.17  |
| absolute difference                                 | 0.05 | 0.02  | 0.015          | 0.1  | 0.04  | 0.03  |
| sanple size in each group                           | 474  | 3313  | 5988           | 219  | 1497  | 2695  |
| total sample size                                   | 948  | 6626  | 11976          | 438  | 2994  | 5390  |
| assuming 20% attrition rate                         | 1138 | 7951  | 14371          | 526  | 3593  | 6468  |
| number needed to treat                              | 20   | 50    | 67             | 10   | 25    | 33    |

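### The stated 6626-13762 patients for 80% power on the primary endpoint joins a total before attrition to one after it; after the assumed 20% loss the lower figure gives about 70% power

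*Protocol*

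**What the plan says.** The Sample Size Calculation, Primary composite outcome, sets out to give a 2-year study "80% power with an alpha value of 0.05 to confirm the superiority of team-based structured care over usual care". It varies the annual usual-care rate from 0.01 to 0.10 and the hazard ratio from 0.5 to 0.85, and assumes an attrition rate of 0.2. For annual rates of 0.05 (high risk) and 0.03 (medium risk) and a hazard ratio of 0.8, it concludes that "a sample size of 6626-13762 patients will give the study 80% power at an alpha value of 0.05".

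The table below that text is headed "80% power at 0.05 alpha". Each block has a per-group size, a total, and a total with 20% attrition, for hazard ratios 0.5, 0.8 and 0.85 in that order:

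- High risk, total before attrition: "948 | 6626 | 11976". The attrition row for hazard ratio 0.8 reads 7951.
- Moderate risk, per group: "1067 | 5734 | 13820".
- Moderate risk, total with attrition: "2561 | 13762 | 33168".

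The Secondary composite outcome tables have the same layout. For attaining two ABC goals, the text gives 295-1814 patients after 20% attrition. Data Analysis fixes the test as two-sided: "A p value of 0.05 or less (2-tailed) will be considered significant".

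**The concern.** The sentence with the range is the protocol's statement of how many patients the primary comparison needs in high- and medium-risk patients. The paragraph says attrition was allowed for, so a reader takes both ends as numbers to randomise. Only the upper end is. Someone who plans on 6626 would believe that the power is 80% after losses when the protocol's own assumptions give clearly less.

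The attrition step and two of the moderate-risk cells also looked inconsistent with the stated 20% loss and the stated 80% power. A correction of the range should therefore cover the whole set of tables.

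**Working it through.** **Inputs.** Two-sided alpha 0.05 (Data Analysis); power 80% (table heading); 1:1 allocation (Setting and Patients); 2-year proportions from the table, for example 0.10 v 0.08 (high risk, hazard ratio 0.8) and 0.06 v 0.048 (moderate risk, hazard ratio 0.8); attrition 0.2.

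**Step 1: reproduce the table.** The protocol does not name its formula. The pooled two-proportion formula with continuity correction fits. With d = |p1 − p2| and p̄ = (p1 + p2)/2:

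- n′ = [1.96·√(2p̄(1−p̄)) + 0.8416·√(p1(1−p1) + p2(1−p2))]² / d²
- n = (n′/4)·[1 + √(1 + 4/(n′d))]²

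For 0.10 v 0.08: n′ = (1.96·0.40472 + 0.8416·0.40447)²/0.02² = 3212.9, so n = 3312.2, that is 3313 per group and 6626 in total, as printed. For 0.06 v 0.048: n = 5733.1, that is 5734 per group and 11468 in total, as printed. Across the primary table (15 cells) and the secondary tables (11 cells), 24 of 26 per-group sizes reproduce at 80% power.

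**Step 2: locate the two ends of the range** (hazard ratio 0.8).

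| | Before attrition | Protocol's attrition row (×1.2) | Total/0.8 |
|---|---|---|---|
| High risk (0.05 per year) | **6626** | 7951 | 8283 |
| Moderate risk (0.03 per year) | 11468 | **13762** | 14335 |

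The range printed in the text uses the two bold entries, which lie in different columns.

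**Step 3: power at 6626 randomised with 20% lost.** Per group, m = 6626 × 0.8 / 2 = 2650.4. The continuity correction reduces this to m(1 − 1/(md))² = 2551.3. Then z = (0.02·√2551.3 − 1.96·0.40472)/0.40447 = 0.536, which is power 70.4%. Without the correction, z = (0.02·√2650.4 − 1.96·0.40472)/0.40447 = 0.584, which is 72.0%.

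**Step 4: the attrition factor.** All 26 attrition entries equal total × 1.2, rounded (for example 17520 → 21024, 6626 → 7951, 1512 → 1814). Losing 20% of 1.2N leaves 1.2 × 0.8 N = 0.96N. Retaining N needs N/0.8 = 1.25N. For 13762 randomised, 5504.8 per group remain, and power for 0.06 v 0.048 is 78.3% corrected or 79.6% uncorrected. Over the 24 cells sized at 80%, power after loss is about 78% corrected (78.2-78.6%) and 79.2-83.6% uncorrected.

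**Step 5: the two cells that do not reproduce.**

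| Moderate risk | Printed per group | Formula at 80% | Formula at 90% |
|---|---|---|---|
| 0.06 v 0.03 (hazard ratio 0.5) | 1067 | 813.7 | 1067.0 |
| 0.06 v 0.051 (hazard ratio 0.85) | 13820 | 10378.8 | 13819.2 |

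Both match 90% power, while the cell between them (5734) is at 80%. They exceed the 80% sizes by 1067/814 = 1.31 and 13820/10379 = 1.33. After the ×1.2 step and 20% loss they still have about 89% power (88.7% and 88.8%, corrected).

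**The case against.** **The ×1.2 error is small.** This stands. The 78% figure depends on the continuity correction, and Data Analysis names a chi-squared test without mentioning one. Uncorrected, the hazard ratio 0.8 rows of the primary table miss 80% by half a point or less, and many other cells stay above it. That is minor beside inputs that span hazard ratios 0.5-0.85 and annual rates 0.01-0.10.

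**Lost patients are not worthless.** The plan uses Kaplan-Meier analysis, includes anyone with one visit or phone contact after randomisation, and seeks yearly status from patients who miss repeat assessments. This also stands. If lost patients contribute partial follow-up, power at 6626 lies somewhere between 70% and 80%. It does not rescue the range, because the protocol itself adjusts for attrition at one end and not at the other.

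**Readings that go too far.** A reader might infer that no attrition-inflated total reaches 80% power. The two 90% cells do so comfortably, and so do many others without the correction. A reader might infer that the 80% figures are wrong throughout; 24 of the 26 per-group sizes before attrition are right. A reader might also infer that recruitment was set on wrong numbers. The documents do not support that: the primary table is a grid of scenarios, what is fixed is 600 per site, and the protocol justifies 600 from the secondary risk-factor calculations. No cell in any of the tables crosses 600 because of the correction. For example, the average two-ABC-goal case moves from 446 to 465, and the 5% body-weight cell was already above 600 at 614.

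**Conclusion.** The range is wrong as written. Its lower end omits the attrition that the same paragraph assumes, and 6626 randomised gives about 70% power (72% uncorrected) instead of 80%. On the protocol's own inputs the consistent attrition-adjusted range is 8283-14335, so the lower end rises by 25% (8283/6626) and the upper end by 4% (14335/13762).

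The other two errors are secondary. The attrition rows fall 4% short of keeping their printed totals, which costs under 2 points of power with the continuity correction in the 24 correctly sized cells. The two 90%-power cells err upward, are not quoted in the text and lie outside the hazard ratio 0.8 range.

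The 70% and 78% figures assume that the continuity-corrected two-proportion method inferred from the table is the one used, and that patients lost contribute nothing. The mixed rows and the ×1.2 factor need neither assumption; both can be read directly from the tables.

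**What to change.** 1. In the primary outcome text, replace the range by 8283-14335 randomised, and say that it includes 20% attrition.
2. In the moderate-risk block, first replace 1067 and 13820 by 814 and 10379 per group (totals 1628 and 20758). Dividing the printed totals by 0.8 without this step would carry the 90% values forward.
3. Then recompute every attrition row as total/0.8, rounded up:

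| Primary table, hazard ratio | 0.5 | 0.8 | 0.85 |
|---|---|---|---|
| Very low risk (0.01) | 6288 | 44595 | 80833 |
| Low risk (0.02) | 3098 | 21900 | 39670 |
| Moderate risk (0.03) | 2035 | 14335 | 25948 |
| High risk (0.05) | 1185 | 8283 | 14970 |
| Very high risk (0.10) | 548 | 3743 | 6738 |

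For two ABC goals the entries become 308, 465 and 1890, and the text range 295-1814 becomes 308-1890. The eight risk-factor columns follow by the same division.

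4. Name the sample-size formula and say whether it includes the continuity correction.

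The cost is a correction of text and tables. Most attrition-adjusted entries rise by about 4%, and the two moderate-risk entries fall (2561 to 2035, 33168 to 25948). Design, conduct and the 600 per site are not changed by it.
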